## Abstract

**Background:**

Post-stroke spasticity (PSS) is a common motor complication during stroke recovery, imposing a substantial burden on both individuals and society owing to its high morbidity and disability rates. Current evidence suggests that acupuncture may be an effective intervention for alleviating PSS; however, the efficacy and safety remain uncertain owing to methodological limitations and the generally low quality of the existing evidence. Therefore, this study aims to evaluate the efficacy, feasibility, and safety of acupuncture for PSS and to explore the underlying anti-spasticity mechanisms.

**Methods:**

This study is a prospective, randomized, controlled trial. A total of 180 patients diagnosed with post-stroke spasticity (PSS) will be enrolled and randomly assigned in a 1:1:1 ratio to one of the three groups: acupuncture, sham acupuncture, or the basic treatment group. Participants in the acupuncture and sham acupuncture groups will receive a 4-week intervention, followed by a 4-week follow-up period. In contrast, the basic treatment group will receive only conventional medical management and standardized rehabilitation training without any acupuncture-related procedures. The primary outcome measure will be spasticity severity, assessed using the Modified Ashworth Scale (MAS). The secondary outcomes will include motor function (Fugl-Meyer Assessment, FMA), clinical spasticity (Clinical Spasticity Index, CSI), neurological impairment (National Institutes of Health Stroke Scale, NIHSS), activities of daily living (Modified Barthel Index, MBI), neuromuscular activity (surface electromyography, sEMG), and muscle mechanical properties (ultrasonographic elastography, UE). The FMA, CSI, NIHSS, and MBI will be evaluated at baseline, week 2, week 4 (end of treatment), and the 4-week follow-up visit. The MAS, sEMG, and UE will be assessed at baseline and at the end of the 4-week treatment period.

**Discussion:**

The results of this trial will help to clarify the preliminary efficacy, clinical feasibility, and safety of acupuncture for PSS patients and explore the anti-spastic mechanisms of acupuncture.

**Clinical trial registration:**

https://itmctr.ccebtcm.org.cn/mgt/project/view/1963190034123325440, ITMCTR2025001662.

## Introduction

1

Stroke is the second leading cause of death from non-communicable diseases (NCDs) and the third leading cause of disability-adjusted life-years (DALYs) globally (1). Stroke-induced motor dysfunction manifests in diverse forms, including paresis/weakness, spasticity, impaired motor control, and abnormal synergies. Among these impairments, spasticity is a prevalent and clinically significant feature during stroke recovery and is considered a hallmark of upper motor neuron syndrome (2). A literature review reveals that the median time to onset of post-stroke spasticity (PSS) is 34 days following the index stroke event (3). In the chronic phase, spasticity affects up to 97% of stroke survivors, with moderate to severe motor impairment (4). Given its high prevalence and chronic nature, PSS substantially increases therapeutic complexity, markedly impairs activities of daily living (ADLs), and imposes a considerable burden on both caregivers and healthcare systems. Therefore, elucidation of the underlying pathogenic mechanisms and development of safe, effective, and evidence-based interventions for PSS represent critical unmet clinical needs.

Originally proposed in 1980, the clinical term “spasticity” was defined by J. W. Lance as “a motor disorder characterized by a velocity-dependent increase in tonic stretch reflex activity (i.e., muscle tone) and exaggerated tendon jerks, resulting from hyperexcitability of the stretch reflex—a key feature of the upper motor neuron syndrome (UMNS)” (5). Owing to the complexity of its pathogenic factors, several hypotheses have been proposed regarding the pathogenesis of PSS. Current evidence indicates that spasticity reflects aberrant neural plasticity arising from disrupted sensorimotor integration; specifically, hyperactive stretch reflexes enhance neuronal excitability, thereby accelerating the progression of spasticity (6). Additional contributors, including passive muscle stretching, local inflammation, and tissue injury, can alter the biomechanical properties of skeletal muscles and tendons. These changes increase the sensitivity of muscle spindles and other proprioceptive receptors, thereby enhancing sensorimotor feedback, increasing motor neuron firing rates, and promoting hypersensitivity responses of muscles and tendons to sensory stimuli, which collectively exacerbate spasticity (7). Furthermore, the increased release of neurotransmitters, such as glutamate (Glu), acetylcholine (ACh), and 5-hydroxytryptamine (5-HT), can prolong involuntary muscle contractions and extend the duration of spasticity (8).

Treatment of PSS focuses on the control of spasticity and improvement of motor function, with an emphasis on early intervention (within 3 months after stroke). Current therapeutic approaches encompass both pharmacological and non-pharmacological modalities. Pharmacological interventions include intramuscular botulinum toxin injections and oral anti-spasmodic agents such as baclofen; non-pharmacological options include acupuncture, exercise therapy, mirror therapy, and extracorporeal shock wave therapy (9). Baclofen, a *γ*-aminobutyric acid (GABA)-b agonist, is the most commonly used oral anti-spasmodic with generally good efficacy, but it has certain adverse effects, including drowsiness, fatigue, hepatotoxicity, and, in some cases, paradoxical muscle weakness (10). Botulinum toxin type A (BoNT-A) intramuscular injection is an effective therapy for relieving spasm-related pain; however, its high cost may limit its wider application (11). Given the limitations of existing anti-spasticity agents, there is a pressing need to investigate new therapeutic strategies that can simultaneously enhance efficacy and improve safety in treating PSS patients.

Research indicates that acupuncture ameliorates motor dysfunction by activating the primary motor cortex (M1) of the ipsilesional hemisphere and promoting brain network remodeling in motor-related areas (12). Acupuncture is currently used to treat PSS. Clinical evidence suggests that acupuncture can alleviate spasticity, enhance motor function, and accelerate rehabilitation and has received a Grade B recommendation for PSS management (13). Experimental studies indicate that acupuncture ameliorates PSS through multiple mechanisms. It modulates the Glu/GABA–glutamine (Gln) cycle via glutamate transporter 1 (GLT-1), thereby rebalancing Glu/GABA levels and mitigating spinal hyperreflexia (14). In addition, it enhances cerebral blood flow in the ischemic penumbra and restores spinal inhibitory control via 5-hydroxytryptamine receptor 2A (5-HT_2A_R)-dependent potassium–chloride cotransporter 2 (KCC2) reactivation, thereby improving limb spasticity (15). However, the majority of the studies are of low methodological quality and lack standardized acupuncture protocols and rigorous study designs. In addition, the potential placebo effects remain incompletely characterized, which may hinder definitive conclusions. Further high-quality research is essential to validate the efficacy and safety of acupuncture for PSS and to elucidate the underlying neuromuscular mechanisms, providing more reliable, evidence-based guidance for personalized prophylaxis and therapy for PSS.

As a solution, we designed a pilot randomized controlled trial (RCT) to assess the preliminary efficacy, feasibility, and safety of acupuncture for PSS and explore the underlying anti-spasticity mechanism of acupuncture.

## Methods and design

2

### Study design

2.1

This study is a 4-week randomized controlled trial, in which 180 participants will be randomly allocated to three groups in a 1:1:1 ratio. The trial will be conducted from December 2024 to December 2026 at Dongzhimen Hospital, Beijing University of Chinese Medicine. Both the acupuncture and sham acupuncture groups will receive standard conventional therapy and rehabilitation training, along with 12 sessions of acupuncture (administered three times per week) over a 4-week treatment period. The control group—referred to as the basic treatment group—will receive only conventional therapy and rehabilitation training during the 4-week intervention period, without any acupuncture. As compensation, the participants in this group will receive 12 sessions of acupuncture after an 8-week follow-up period. The trial protocol will be based on the Standard Protocol Items: Recommendations for Interventional Trials (SPIRIT) checklist. This study has been approved by the Ethics Committee of Dongzhimen Hospital, Beijing University of Chinese Medicine, and has been prospectively registered with the International Traditional Medicine Clinical Trial Registry (ITMCTR). The study flowchart is presented in Figure 1, and the timeline for participant enrollment, interventions, and outcome assessments is detailed in Table 1.

**Figure 1 fig1:**
[figure not shown]
Study flowchart. MAS, Modified Ashworth Scale; CSI, Clinical Spasticity Index; NIHSS, National Institutes of Health Stroke Scale; FMA, Fugl-Meyer Motor Assessment; MBI, Modified Barthel Index; sEMG, Surface Electromyography; SWUE, Shear-wave ultrasound elastography.

**Table 1 tab1:** Schedule of enrollment, interventions, and assessments.

Time points	Enrollment	Baseline	Treatment period				Follow-up period	
	Week 1	Week 0	Week 1	Week 2	Week 3	Week 4	Week 6	Week 8
Screening and recruitment								
Inclusion and exclusion	x							
Clinical interview	x							
Sign the informed consent	x							
Randomization		x						
Interventions								
Acupuncture group			12 sessions of treatment (3 times a week)					
Sham acupuncture group			12 sessions of treatment (3 times a week)					
Basic treatment group			No acupuncture treatment					
Assessments								
MAS		x		x		x	x	x
FMA		x		x		x	x	x
CSI		x		x		x	x	x
NIHSS		x		x		x	x	x
MBI		x		x		x	x	x
sEMG		x				x		
SWUE		x				x		
Others								
Adverse events			x	x	x	x		
Blinding assessment			x	x	x	x		
Patients’ compliance			x	x	x	x		
Type of stroke		x						
Patients’ complications		x						

MAS, Modified Ashworth scale; FMA, Fugl-Meyer motor function assessment; CSI, comprehensive spasticity scale; NIHSS, National Institutes of Health Stroke Scale; MBI, Modified Barthel Index; sEMG, surface electromyography; SWUE, Shear-wave ultrasound elastography.

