### Patient adherence

2.4

To ensure the completion of the trial, measures must be implemented to enhance patient compliance. First, researchers will comprehensively review the pathophysiology, diagnostic criteria, and current treatment strategies for PSS prior to trial initiation and ensure comprehensive empathetic communication with participants to establish mutual trust. Second, we will inform patients that acupuncture treatment is conducted on the basis of conventional treatment and rehabilitation training and it does not endanger their health to mitigate the participants’ concerns. Third, all acupuncturists involved in the trial will receive professional and standardized training before enrollment to ensure proficiency. Furthermore, all acupuncture treatments will be performed by a designated certified acupuncturist to guarantee that the patients have a favorable experience. Additionally, our research team will maintain regular, transparent communication with participants and their caregivers to foster a shared understanding of the patient’s clinical condition and encourage them to receive active engagement in the acupuncture treatment. Patients will be clearly informed that all trial-related examinations (such as surface electromyography (sEMG) and shear-wave ultrasound elastography), scale assessments, and 12 acupuncture treatments are free of charge. Finally, all adverse events and participant dropouts during the trial will be documented.

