### Safety and adverse events

2.8

The acupoints selected in this trial are based on a consensus among acupuncture experts and are considered relatively safe. Potential adverse events included pain, numbness, subcutaneous swelling, bruising, fainting during acupuncture, needle sticking, or needle bending. If an adverse event occurs, it will be recorded in detail in the Case Report Forms (CRFs). Serious adverse events, such as syncope, deep tissue infection, or abscess, will be promptly reported to the Ethics Committee, and affected participants will be immediately withdrawn from the trial and provided with active and effective treatment.

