### Quality control and data management

2.10

Outcome assessors will collect all participant data using paper-based CRFs and subsequently enter the data into an electronic database. The research team will conduct periodic data monitoring to verify completeness, accuracy, and authenticity while concurrently tracking trial progress and adherence to the intervention protocol. To enhance adherence, researchers will maintain regular contact with the participants via telephone or WeChat, providing reminders to actively engage in treatment, scheduled assessments, and follow-up visits. All adverse events and reasons for participant discontinuation—whether from the trial or from follow-up—will be systematically documented.

Acupuncturists, outcome assessors, and statisticians will all receive standardized training on the study protocol to ensure a full understanding of the study procedures and details. Specifically, acupuncturists will complete comprehensive professional training covering acupoint selection and localization, acupuncture techniques, treatment frequency and duration, and distinct protocols for both verum and sham acupuncture, thereby ensuring intervention consistency and fidelity across all participants. All members of the research team will attend scheduled organizational meetings every three weeks to review the progress, identify challenges, and collaboratively resolve issues arising during the trial.

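### Table 1 schedules no adverse-event check at either follow-up visit (weeks 6 and 8), although the text promises that all adverse events will be documented

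*Protocol article*

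**What the plan says.** Table 1 (Schedule of enrollment, interventions, and assessments) has a row headed "Adverse events". It is marked in each of the four treatment weeks and in neither follow-up column. In the same table MAS, FMA, CSI, NIHSS and MBI are all marked at weeks 6 and 8.

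Three places in the text deal with recording harm:

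- Section 2.4 (Patient adherence): "all adverse events and participant dropouts during the trial will be documented".
- Section 2.8 (Safety and adverse events): "If an adverse event occurs, it will be recorded in detail in the Case Report Forms (CRFs"). No time window is given. The section then names the events that go promptly to the Ethics Committee: "Serious adverse events, such as syncope, deep tissue infection, or abscess".
- Section 2.10 (Quality control and data management): "All adverse events and reasons for participant discontinuation—whether from the trial or from follow-up—will be systematically documented".

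On timing, the Abstract says that the two needling arms "will receive a 4-week intervention, followed by a 4-week follow-up period". Section 2.1 gives "12 sessions of acupuncture (administered three times per week) over a 4-week treatment period", so the last sessions fall in week 4.

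**The concern.** Safety is a stated aim in the Abstract, the Introduction and the Conclusion. A schedule that ends harm collection with the last treatment week does not deliver the systematic record of all events that the text promises.

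Some of the listed harms occur during needling, such as fainting or a stuck or bent needle, and weekly checks during treatment should catch them. Deep tissue infection and abscess need not be apparent at the session. After a week-4 session such an event may first show itself when no check is scheduled, although the participant is due to be seen twice more. The safety record could then be incomplete for the second half of observation.

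**Working it through.** The protocol article states no figure to reproduce here, so the check sets the places side by side and adds a simple count.

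**Step 1: is the row intact?** Read by column, it has empty cells for enrollment and baseline, marks at weeks 1, 2, 3 and 4, and empty cells for weeks 6 and 8. The scale rows above carry marks in those last two columns, so the columns survived text extraction. A broken table is an unlikely explanation for the blanks.

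**Step 2: count the coverage.**

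- Post-baseline time points in Table 1: weeks 1, 2, 3, 4, 6 and 8, which is 6. Marked for adverse events: 4 of 6.
- Follow-up time points: weeks 6 and 8, which is 2. Marked for adverse events: 0 of 2.
- Time after baseline: 4 weeks of treatment + 4 weeks of follow-up = 8 weeks. With scheduled checks: 4/8 = 50%. Without: 4/8 = 50%.

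**Step 3: are participants available at follow-up?** Yes. Table 1 marks five scales at weeks 6 and 8. The Abstract and section 2.7.2.6 independently place FMA, CSI, NIHSS and MBI in follow-up. No new visit is needed to ask about harm.

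**Step 4: compare schedule and text.**

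| Place | What it covers | Limit at week 4? |
|---|---|---|
| Table 1 | Scheduled checks, weeks 1 to 4 | Yes, by the blank cells |
| Section 2.4 | All events during the trial | No |
| Section 2.8 | Any event that occurs goes on the case report form | No |
| Section 2.10 | All events, systematically | No; the same sentence names follow-up |

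In section 2.10 the reference to follow-up grammatically qualifies discontinuation, not adverse events. It still shows that follow-up is within what the study team means to document.

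**Step 5: could the trial mean the four treatment weeks only?** Section 2.1 does call the study a 4-week trial, and on that reading section 2.4 would agree with Table 1. But the Abstract describes a follow-up period after the intervention, and Table 1 places follow-up inside the study schedule. The phrase makes section 2.4 less clear without removing the conflict.

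**The case against.** The strongest reply is that Table 1 lists routine checks, while sections 2.4, 2.8 and 2.10 govern what is done when an event occurs, so both can hold. Section 2.8 has no cut-off, and section 2.10 provides regular telephone or WeChat contact that extends to reminders of follow-up visits. A participant with an abscess in week 5 therefore has a route into the case report form. This stands in part. A reader might infer from the blank cells that late events will not be recorded at all, and the document does not support that. What is missing is scheduled ascertainment. The contact in section 2.10 is described as reminders, not as questions about harm, and reliance on spontaneous reports is not systematic documentation.

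A second reply is that Table 1 is loosely filled in. It marks MAS at weeks 2, 6 and 8, while the Abstract and section 2.7.2.6 place MAS at baseline and week 4 only. It marks the blinding assessment in all four treatment weeks, while section 2.9 describes one assessment after the final session. The blanks may therefore be an oversight and not a decision to stop safety collection. That is plausible, but section 2.1 points the reader to Table 1 for the timeline of outcome assessments, and a schedule printed in error still needs correcting.

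A third reply is that the full protocol and case report forms are not shown and may contain follow-up safety questions. They may. The point here rests on what the article prints: a schedule that does not match its text.

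Two stronger readings are also tempting. A reader might infer that harm is undercounted only in the arm whose skin is penetrated, which would bias the safety comparison toward acupuncture. The blanks apply to all three arms, so other late events go unscheduled in each of them, and no event rates are given. A reader might also want a percentage of events missed. That needs an onset delay for infection or abscess and a base rate, and the document gives neither.

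**Conclusion.** The point holds as a gap in scheduled safety ascertainment and a mismatch between Table 1 and the text. Adverse-event checks are scheduled at 0 of 2 follow-up visits, so 4 of the 8 weeks after baseline rely on spontaneous reporting. The week count rests on the Abstract and Table 1.

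Delayed needle-related events would mainly concern the acupuncture arm, because section 2.6.2 describes the sham needle as non-penetrating and the basic treatment arm receives no needling before follow-up ends. That gives a possible direction for bias in this class of event. Its size is unknown, and a net bias across all adverse events is not shown. The consequence is limited to the completeness of the safety data. For a trial with safety among its aims the correction should be made, but it does not undermine the trial.

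**What to change.** - Add adverse-event marks at weeks 6 and 8 in Table 1.
- Ask the same open question about adverse events at those visits in all three arms.
- Report adverse events by arm through week 8.
- State the collection window once, and bring Table 1 and sections 2.4, 2.8 and 2.10 into line with it.

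The cost is one more case report form item at visits that already take place. The safety figures may look slightly less favourable than with collection ending at week 4. Treatment and the efficacy assessments do not change.

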### Participants

2.2

#### Inclusion criteria

2.2.1

Participants who meet all conditions will be considered for enrollment. The inclusion criteria are as follows: (1) a diagnosis of ischemic or hemorrhagic stroke confirmed by cranial CT/MRI. (2) First-time stroke or recurrent stroke without residual neurological impairment. (3) Duration: 2 weeks to 6 months after stroke onset. (4) Male or female patients aged between 35 and 75 years. (5) Patients met the diagnostic and assessment criteria for PSS: muscle stiffness, shortening, and fixed joint contractures, with grades 1–3 assessed by the Modified Ashworth Scale (MAS) (16). (6) A National Institutes of Health Stroke Scale (NIHSS) score between 4 and 16. (7) Conscious patients (Glasgow Coma Scale score = 15) are able to participate in medical interviews, physical examinations, instructions, and treatment. (8) Patients who agreed to participate in the trial and provided written informed consent.

#### Exclusion criteria

2.2.2

Patients with any one of the following criteria will be excluded from the trial: (1) patients with severe cardiovascular diseases, such as decompensated heart failure (New York Heart Association [NYHA] class III-IV), myocardial infarction (within the last 6 months), or unstable angina pectoris. (2) Immunological/hematological diseases: active autoimmune disease requiring long-term immunosuppression (e.g., >10 mg/day prednisone-equivalent dose) or uncontrolled coagulopathy (e.g., International Normalized Ratio [INR] > 3.0, not at the therapeutic goal of anticoagulation). (3) Malignant tumors. (4) Patients with neurological system diseases that have an obvious impact on this trial, such as Parkinson’s disease, convulsive epilepsy, traumatic brain injury (TBI), or severe neuromuscular disorders. (5) Patients with rheumatoid arthritis, fractures, or other trauma that may confound the efficacy assessment. (6) Patients have received anti-spasticity medications within the past 1 month, such as baclofen, dantrolene, tizanidine, and botulinum toxin. (7) Patients who are allergic to acupuncture or have a history of severe allergic predisposition. (8) Female patients who are pregnant, breastfeeding, or planning pregnancy during the trial period. (9) Patients enrolled in other acupuncture or pharmacotherapy trials.

